## Design and methodology

### Design

This is a randomised, controlled, four-arm parallel groups design. However, given the nature of the interventions, this study is not blinded as both investigators and participants will clearly know what the intervention is, as participants in the lifestyle arms will be actively working towards maintaining the lifestyle change. Participants will be randomly allocated to one of the following four groups:ControlExercise interventionDietary interventionCombined dietary and exercise intervention

The randomisation sequence will be created by permuting into blocks of 4. While allocation of participants to these groups will be randomised, for reasons of practicality, and to avoid cross contamination between the requirements of each group, when cohabiting couples participate, one person will be randomly allocated to a group and the other will be allocated to the same group.

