## Participants

In total, 148 participants who live independently in aged care facilities across a minimum of 15 sites, and who are aged between 60 and 90 years, will participate in this study. These residents live in their own unit or similar accommodation, and are generally physically and mentally capable of caring for themselves in all aspects of daily living. The independent aged care resident population was selected due the generally greater homogeneity of the population and living conditions than that found in the broader community. Furthermore, by focusing on independent living in aged care facilities, this research aims to examine the efficacy of programs aimed at minimising cognitive decline and reducing the rate of transfer to low and high care accommodation.

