### Eligibility criteria

To be eligible to participate in the study, participants must be able to speak and read English fluently. Those who are not taking vitamins or herbal supplements as part of a regular regime will be asked to discontinue their use for the duration of the trial, while those who regularly take such vitamins or supplements will be asked to continue taking them in the same manner for the length of the trial. Finally, participants will be required to get the approval of their General Practitioner before random allocation and commencement.

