## Procedure

Eligible participants will be assessed over four sessions at their living facility. An overview of these sessions is provided in the trial flow diagram (Fig. 1). During the first session, which takes place in the participant’s home, participants are screened for eligibility and assessed with the MMSE and the GDS. Eligible participants are requested to visit their doctor to obtain consent to participate and then to have blood taken for biomarker analysis. Session 2, conducted in a central treatment room in that participant’s living facility, is undertaken once doctor’s consent and blood biomarkers have been obtained. During this visit baseline assessment of all measures are undertaken and participants are informed of the group they have been randomly allocated to. The third session, an in home visit at the 3 month time point, will collect participant recorded diet and/or exercise data where appropriate, and any adherence issues will be discussed. Mood, exercise and sleep questionnaires will also be undertaken at this session. As shown in Fig. 1, the final session will be a full assessment visit, assessing all measures. This will be conducted in a central treatment room of the facility at the 6 month time point. Participant recorded exercise and diet data will also be collected during this session, enabling the investigators to estimate adherence to the intervention.

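### Fixed blocks of 4 for four arms in an open trial are the most predictable permuted blocks possible, which leaves an avoidable opportunity for selection bias at enrolment

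*Protocol article*

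**What the plan says.** The Design section gives the three features that matter. The trial has four arms: "This is a randomised, controlled, four-arm parallel groups design". The block size is a single fixed value: "The randomisation sequence will be created by permuting into blocks of 4". Nobody is masked: "this study is not blinded as both investigators and participants will clearly know what the intervention is". The same section adds a rule for cohabiting couples, under which "one person will be randomly allocated to a group and the other will be allocated to the same group".

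The Sample size section sets equal arms, 37 in each and 148 in total. The Participants section spreads recruitment "across a minimum of 15 sites". The article does not say whether there is one sequence for the whole trial or one per site, or whether a couple takes one slot in the sequence or two.

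**The concern.** Permuted blocks keep arm sizes close, but towards the end of a block they give information away. How much depends on the block length relative to the number of arms, and on whether past allocations can be seen. Here the block length equals the number of arms, and past allocations are visible because the trial is open. Both features are stated in the article, so the point does not rest on anything it leaves out.

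At stake is the comparability of the arms. If someone involved in recruitment can foresee the next arm, the decision on whom to enter next may be influenced, deliberately or not. Both interventions depend on the participant's own effort. Differences in motivation between arms would therefore matter, and adjusting for measured baseline variables would not fully remove them.

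**Working it through.** **Inputs.** Four arms, block size 4 and no blinding (Design); 148 participants, 37 per arm, equal allocation (Sample size); at least 15 sites (Participants).

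**The plan's own figure.** A one-way ANOVA with four groups, f = 0.30 and two-sided 5% level reaches power 0.810 at N = 128, and 128 × 1.15 = 147.2, which with equal arms becomes 148. The sample size reproduces. The present point does not depend on it; 148 serves only to turn shares into counts.

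**Predictability of a fixed block of 4.** Each block is a random ordering of the four arms. After k − 1 open allocations in a block, 5 − k arms remain and are equally likely, so the chance of a correct guess at position k is 1/(5 − k):

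| Position in block | Arms still possible | Chance of a correct guess |
|---|---|---|
| 1 | 4 | 0.250 |
| 2 | 3 | 0.333 |
| 3 | 2 | 0.500 |
| 4 | 1 | 1.000 |

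Mean = (0.250 + 0.333 + 0.500 + 1.000)/4 = 2.083/4 = 0.521. Without any information the chance is 1/4 = 0.25.

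The fully determined share is one slot in four, or 25%. If all 148 participants took their own slot, that would be 148/4 = 37 determined slots and another 37 with two arms left. These are counts of slots, not strictly of people. If a couple uses one slot there are fewer than 148 slots, although the 25% share stays.

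**What longer fixed blocks would do.** With a known fixed size, a slot is determined when all remaining entries of the block are the same arm.

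- Size 8 (each arm twice): (1 + 1/7)/8 = 14.3%.
- Size 12 (each arm three times): (1 + 2/11 + (2/11)(1/10))/12 = 1.2/12 = 10.0%.

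**What varying sizes would do.** Sequences of 148 slots were simulated 4,000 times, with a guesser who always names the arm least used so far and breaks ties at random:

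| Scheme | Correct guesses |
|---|---|
| Fixed 4 | 52.1% |
| Random 4 and 8 | 48.6% |
| Random 4, 8 and 12 | 46.1% |

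The fixed-4 result agrees with the exact value above. The fall in average guessing is modest. The more useful change is that, with undisclosed varying sizes, the observer does not generally know where a block ends and so is rarely certain of the next arm.

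**How many allocations an observer must follow.** With one sequence for the trial, the observer must follow allocations in order across at least 15 sites. With one sequence per site, there would be at most about 148/15 = 9.9 participants per site on average, or about two and a half blocks, and the history would be easy to follow.

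**The case against.** The strongest reply is that predictability needs knowledge the article does not place with recruiters. They would have to know the block size and see every earlier allocation in the sequence, in order, across many sites. Investigators in an open trial know what each participant receives; that does not mean any one of them keeps the running list. This stands, and it makes the point conditional. It does not dispose of it: the block size is printed in the article, allocations are open by design, and a sealed or central list hides the next entry without stopping anyone from working it out from the previous ones.

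It can also be said that the change to the block sizes gains little, 52.1% to 48.6% with sizes 4 and 8. That is correct for average guessing, but the average does not capture the loss of certainty at block ends.

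A reader might go further than the text allows in four ways:

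- **Every fourth participant's arm is certain to the investigators.** This holds only for an observer with the full history, and only for slots. It also ignores couples.
- **Staff can choose the order in which residents are allocated.** The article says nothing of the kind. Allocation waits on outside parties, since "participants will be required to get the approval of their General Practitioner before random allocation and commencement".
- **Baseline testing is coloured by knowledge of the arm.** The Procedure section says "During this visit baseline assessment of all measures are undertaken and participants are informed of the group they have been randomly allocated to". This puts testing and disclosure at one visit, and its wording, if anything, names the testing first. The primary outcome is a computerised response time.
- **The list has no independent holder and no release rule.** A condensed article commonly leaves these to the full protocol, so their absence is not a finding.

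**Conclusion.** The concern holds in a limited form. The Design section fixes the most predictable balanced block available for four equal arms, in a trial where allocations are open. For an observer who knows the block size and the earlier allocations in the same sequence, 25% of slots are determined, a further 25% are one of two arms, and the average rate of correct guesses is 52% against 25% by chance.

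This rests on equal allocation, a constant block size of 4 and complete sight of the sequence so far. The figures are the most such an observer could achieve and are not an estimate of what would happen in this trial. The article supports an avoidable opportunity for selection bias at enrolment. It does not support a claim that allocation was or will be subverted, or that baseline measurements are biased. Because the remedy is cheap, the point is worth acting on despite its conditional nature.

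**What to change.** For participants not yet randomised, generate the remaining sequence with randomly varying block sizes that are multiples of 4, for example 4 and 8, or 4, 8 and 12, and do not disclose the sizes to those who recruit. Make the household the unit drawn, so that a couple uses one slot and the couples rule fits the block structure. Possible wording: the sequence is generated by household in permuted blocks of randomly varying size, each a multiple of the number of arms, with the sizes not disclosed to recruiting staff.

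The cost is a regenerated list and one revised sentence. Balance between arms in short runs becomes slightly looser. Balance is then kept in households, so the number of people per arm can drift a little from 37 when couples join. The sample size and the interventions are unaffected.

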## Participants

In total, 148 participants who live independently in aged care facilities across a minimum of 15 sites, and who are aged between 60 and 90 years, will participate in this study. These residents live in their own unit or similar accommodation, and are generally physically and mentally capable of caring for themselves in all aspects of daily living. The independent aged care resident population was selected due the generally greater homogeneity of the population and living conditions than that found in the broader community. Furthermore, by focusing on independent living in aged care facilities, this research aims to examine the efficacy of programs aimed at minimising cognitive decline and reducing the rate of transfer to low and high care accommodation.

### Eligibility criteria

To be eligible to participate in the study, participants must be able to speak and read English fluently. Those who are not taking vitamins or herbal supplements as part of a regular regime will be asked to discontinue their use for the duration of the trial, while those who regularly take such vitamins or supplements will be asked to continue taking them in the same manner for the length of the trial. Finally, participants will be required to get the approval of their General Practitioner before random allocation and commencement.

### Ineligibility criteria

Participants will be unable to participate in the trial if they have any significant visual impairment that would prevent them from reading or performing computer based tasks, have a significant neurological or psychiatric disorder, or are unable to walk independently and safely. Additionally, study participants will not be eligible if taking illicit drugs or cognitive enhancing medications. Finally, those with suspected cognitive impairment (defined as a score ≤ 24 on the MMSE), or a significant level of symptoms of depression (a score > 9 on the Geriatric Depression Scale (GDS)), will also be excluded.

This study was ethically approved by the Swinburne University Human Research Ethics Committee (project number 2013/057) and all participants will provide written consent from both themselves and their general practitioner before commencement in the trial.

## Sample size

To date no studies using specific measures of cognition more sensitive than the MMSE have investigated the cognitive effects of a Mediterranean dietary intervention in the elderly. However, numerous trials have examined the effects of exercise fitness interventions. In a meta-analysis conducted to investigate the potential for fitness training to improve cognition in sedentary, but otherwise healthy, older adults, fitness training increased cognitive performance 0.5 SD on average, regardless of the type of cognitive task or the training method [27]. Using Cohen’s effect size criteria, this represents a medium effect size [65]. Although there are no relevant trials which have focussed on the Mediterranean diet, from which to determine an effect size, we have previously identified slightly larger effect sizes on SUCCAB memory measures following several months combined micronutrient, mineral and herbal supplementation in older people with risk factors for cognitive decline [66, 67]. We would anticipate the dietary change condition may exert many of the same benefits as micronutrient dietary supplementation, therefore a comparable effect size may be anticipated. Power analysis was conducted using GPower 3.1.3 to determine the sample size required for a four armed intervention (exercise change only, diet change only, exercise and diet change, no change) using an analysis of variance (ANOVA) design. It was indicated that a total sample of 128 participants would be required to detect a moderate effect size (*f* = 0.30), power of 80 % and a significance level of 5 %. Based on previous trials conducted by the Swinburne University Centre for Human Psychopharmacology, an allowance for a 15 % drop out from the trial has been factored in. Therefore, a total sample of 148 participants will be recruited for this trial, with 37 individuals randomised to each arm of the study.

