## Aims and study hypotheses

The primary aim of the current study is to examine the 6-month effects of increased exercise through walking, change to a Mediterranean diet, and a combination of both, on cognitive performance in an elderly population living independently in aged care facilities. It is hypothesised that measures of cognitive performance will be improved in both the exercise and dietary interventions, relative to the controls, and that the combined diet and exercise intervention will show the greatest improvement of all groups.

As a secondary aim, this study will also investigate the associations between cognitive function and blood based biomarkers and cardiovascular function, which have been proposed as mechanisms, or indicators of mechanisms, that may influence the rate of cognitive ageing. By investigating these variables, the current study aims to identify and target modifiable risk factors, as well as identifying objective biological indicators of the efficacy of interventions that are aimed at ameliorating the rate of cognitive ageing.

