## Analysis

### Primary outcome

The primary outcome will be response time on the SUCCAB memory measures. Previously benefits to response time on SUCCAB memory measures has been demonstrated following multivitamin [67] and other nutraceutical intervention [68]. Mixed design, repeated measures analysis of co-variance (ANCOVA) will be used to assess treatment-related changes in cognitive performance over the study. Relevant covariates may include group differences in cognitive performance or biomarkers at baseline and co-habitation of participants, where couples are taking part in the intervention trial.

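### The stated 80% power belongs to a four-arm omnibus F test; the hypothesised single-intervention and combined-versus-single contrasts have less, about 51% unadjusted for each single arm versus control

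*Protocol article*

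**What the plan says.** The Aims and study hypotheses section of the protocol article makes two predictions. For the single interventions it reads: "measures of cognitive performance will be improved in both the exercise and dietary interventions, relative to the controls". For the combination it goes further and expects this: "the combined diet and exercise intervention will show the greatest improvement of all groups". The abstract and the closing conclusion repeat that benefit is expected from each intervention alone and from the two together.

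The Sample size section conducted its power analysis "to determine the sample size required for a four armed intervention (exercise change only, diet change only, exercise and diet change, no change". It describes the statistical framework for that calculation only as "using an analysis of variance (ANOVA) design". The total of 128 is given for f = 0.30, with "power of 80 % and a significance level of 5" per cent. After a 15% dropout allowance this becomes 148, or 37 per arm. The one effect size it gives in SD units comes from a meta-analysis in which "fitness training increased cognitive performance 0.5 SD on average, regardless of the type of cognitive task or the training method". For diet it expects something comparable to supplementation effects that it calls slightly larger, without a figure. No power is given for any pairwise comparison.

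Under Analysis, Primary outcome, a mixed-design "repeated measures analysis of co-variance (ANCOVA) will be used to assess treatment-related changes in cognitive performance over the study". Baseline performance is listed among covariates that may be used. Under Analysis, Secondary outcomes, two pooled comparisons are planned as secondary analyses: both diet arms v control and both exercise arms v control.

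**The concern.** A four-group F test asks whether there is some difference among the arms. The hypotheses ask which arms differ, and in which direction. A significant F can come from one component alone, so it cannot by itself support the claim about exercise, the claim about diet or the claim about the combination. If 80% power holds only for the F test, a reader of the Sample size section is told more than the design delivers for the single interventions. Two misreadings would follow: a non-significant single-arm comparison taken as evidence of no effect, and a significant overall test taken as support for every hypothesis.

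**Working it through.** **Inputs from the protocol article.** Four equal arms; f = 0.30; 128 evaluable, so 128/4 = 32 per arm; alpha 5%; exercise effect 0.5 SD; diet effect comparable. Sidedness is not stated, so two-sided 5% is assumed for contrasts.

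**Assumed inputs (no figure in the article).**
- Baseline correlation r: 0.5 to 0.7.
- Diet effect: 0.5 to 0.6 SD.
- Increment of combined over a single intervention: 0.25 to 0.5 SD.
- Where one scenario is needed, arm means (control/exercise/diet/combined) of 0/0.5/0.5/0.84 SD. The value 0.84 is chosen because it brings f to 0.30.

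**1. Reproduce the 128.** For the omnibus F, df = 3 and 124 and the noncentrality is N·f² = 128 × 0.09 = 11.52. Power is 81.0%. With 124 in total it is 79.6%, so 128 is the smallest balanced total reaching 80%. At f = 0.30 the alternatives tried do not give 128: a 1-df F test needs 90, a repeated-measures between-group test (correlation 0.5) needs 96, and a repeated-measures interaction needs 36. The 80% is therefore the power of the 3-df omnibus test.

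**2. Contrasts, unadjusted.** Two-sided noncentral t with pooled error (df 124) and noncentrality d/√(2/32) = 4d:

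| Contrast | d (SD) | 4d | Power |
|---|---|---|---|
| Exercise or diet v control | 0.5 | 2.00 | 51% |
| Diet v control, larger effect | 0.6 | 2.40 | 66% |
| Combined v one single arm | 0.25 | 1.00 | 17% |
| Combined v one single arm | 0.34 | 1.36 | 27% |
| Combined v one single arm | 0.5 | 2.00 | 51% |
| Combined v control | 0.84 | 3.36 | 92% |

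If all 37 per arm were evaluable, a single arm v control at 0.5 SD would have about 57%. Unadjusted 80% power at 0.5 SD needs 64 per arm, or 256 evaluable.

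**3. Contrasts with baseline always in the model.** The residual SD is √(1 − r²), so d becomes 0.5/√(1 − r²):
- r = 0.5: 0.5/0.866 = 0.577, power 63%
- r = 0.6: 0.5/0.8 = 0.625, power 70%
- r = 0.7: 0.5/0.714 = 0.700, power 79%

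At r = 0.8 it would be 91%. Combined v one single arm at a 0.25 SD increment is 21% at r = 0.5 and 38% at r = 0.8.

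**4. Pooled secondary contrasts.** Under 0/0.5/0.5/0.84, either pooled effect is (0.5 + 0.84)/2 = 0.67 SD, with 64 v 32. The noncentrality is 0.67/√(1/64 + 1/32) = 3.09 and power is about 87%.

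**5. What a significant F can mean.** Take means 0/0.6/0/0.6, where exercise works and diet does nothing. The grand mean is 0.3, every arm lies 0.3 from it, and f = 0.30. The F test is significant in 81% of trials, although the hypothesis about diet is false.

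**The case against.** Several stronger readings are tempting, and the document does not support them.

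- A reader might infer that every comparison with control is near 50%. That fails for combined v control, which is about 92% at 0.84 SD and 85% at 0.75 SD. For the same reason it is too strong to say that no hypothesis has 80% power.
- A reader might infer that nothing but an overall test is planned, or that conclusions rest on it. The Analysis section does not say so. It names an ANCOVA without a decision rule and plans pooled 1-df comparisons. Those comparisons are well powered under the means above. However, they are secondary and both contain the combined arm, so neither isolates one component.
- The 51% is unadjusted, while the planned model uses baseline and follow-up data. This objection stands, which is why a range is given. The article states no correlation, makes baseline an optional covariate and takes no credit for it in the sample size.
- The combined-v-single figures depend on assumed increments, and the greatest-improvement hypothesis could be read as a ranking only. Hence the 17% to 51% range. A joint requirement to beat both single arms would be a stricter reading than the text demands.
- Choosing the order of contrasts or a multiplicity method is commonly left to the SAP, and its absence here is no fault.

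The mismatch between the stated power basis and the stated hypotheses remains. A later SAP can name contrasts, but it cannot make the published 80% apply to them.

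**Conclusion.** The point holds as a mismatch between the Sample size section and the Aims and study hypotheses section. The 80% is omnibus power. For a single intervention v control at 0.5 SD, power is about 51% unadjusted and about 63% to 79% with consistent baseline adjustment at an assumed correlation of 0.5 to 0.7. Diet v control reaches about 66% unadjusted only if its effect is 0.6 SD. Combined v one single arm is the weakest comparison, at about 17%, 27% and 51% for assumed increments of 0.25, 0.34 and 0.5 SD. All of these figures take 32 evaluable per arm and two-sided 5% with no multiplicity adjustment. The finding does not extend to combined v control, and it does not say that the omnibus calculation is wrong.

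**What to change.** In Sample size, state that the 80% applies to the omnibus test only, and give power for each hypothesised contrast with the assumed effect and baseline correlation.

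In Analysis, Primary outcome, base the primary conclusions on pre-specified 1-df contrasts: exercise v control, diet v control, combined v control, and combined v each single arm. Take them from one model that always adjusts for the baseline SUCCAB score. The multiplicity rule can be left to the SAP.

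The cost is wording and a less favourable power statement. The change discloses the limited power of the single-arm and combined-v-single contrasts and does not remove it. A multiplicity adjustment lowers it further: Bonferroni for three contrasts (alpha 0.05/3) takes a single arm v control at 0.5 SD from 51% to about 34% without baseline adjustment. No new data are needed.

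### The stated 80% power belongs to f = 0.30, which is not the 0.5 SD effect cited to justify the sample size; the assumed arm means that would connect them are not given

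*Protocol article*

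**What the plan says.** All of the justification is in the Sample size section of the protocol article. The only numerical effect there comes from a meta-analysis of exercise in older adults: "fitness training increased cognitive performance 0.5 SD on average, regardless of the type of cognitive task or the training method". The protocol classifies it: "Using Cohen’s effect size criteria, this represents a medium effect size". For diet it gives no number. It refers to supplementation trials in which "we have previously identified slightly larger effect sizes on SUCCAB memory measures" and expects dietary change to have a comparable effect.

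The calculation that follows is for four arms, "using an analysis of variance (ANOVA) design", with "power of 80 % and a significance level of 5" per cent. Its result is: "It was indicated that a total sample of 128 participants would be required to detect a moderate effect size", and the size entered is f = 0.30. After a dropout allowance the target is 148, or 37 per arm.

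Aims and study hypotheses expects each single intervention to beat control and the combined arm to do best. It does not say by how much.

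**The concern.** The paragraph moves from a standardised difference of 0.5, labelled medium, to f = 0.30, labelled moderate, as if they were the same assumption. They are on different scales. Cohen's f for four arms is the standard deviation of the four arm means in within-arm SD units, so it depends on all four means. The protocol states none of these beyond the 0.5 SD for exercise and a comparable, unquantified effect for diet.

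The 80% will be read as the chance of detecting the effect that the paragraph argues for. If that chance is materially lower under arm means consistent with the text, a non-significant result could be taken as stronger evidence against a 0.5 SD benefit than the design supports. The comparisons of each single intervention with control, which the hypotheses name, are exposed in the same way.

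**Working it through.** **Inputs.** From the Sample size section: four equal arms, alpha 5%, f = 0.30, N = 128 evaluable (32 per arm), cited effect 0.5 SD. Assumption: the 0.5 SD is a difference from control in within-arm SD units.

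**Formulas.** f = square root of the mean squared deviation of the four arm means from their average. Omnibus power comes from the non-central F distribution with df1 = 3, df2 = N − 4 and noncentrality N × f².

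**1. The protocol's own figure.** At f = 0.30 and N = 128 the noncentrality is 128 × 0.09 = 11.52 and power is 81.0%. The smallest N giving 80% is 126, which becomes 128 with equal arms. The 128 reproduces.

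**2. What 0.5 SD gives as f.** Arm order: control, exercise, diet, combined.
- 0 / 0.5 / 0.5 / 0.5: average 0.375; squared deviations 0.1406 + 3 × 0.0156 = 0.1875; divided by 4 = 0.0469; f = 0.217. Noncentrality 6.0; power 50.4%. For 80%, N = 240.
- 0 / 0.5 / 0.5 / 0.75: average 0.4375; squared deviations sum to 0.2969; f = 0.272; power 72.2%.
- 0 / 0.5 / 0.5 / 0.84: average 0.46; squared deviations sum to 0.3592; f = 0.300; power 80.9%.
- 0 / 0.5 / 0.5 / 1.0 (fully additive): average 0.5; squared deviations sum to 0.5; f = 0.354; power 92.6%.

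For two equal groups f = d/2, so 0.5 SD corresponds to f = 0.25. Used in the four-arm test, f = 0.25 gives 63.9% at N = 128 and needs N = 180 for 80%.

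**3. What f = 0.30 requires.** If all active arms are equal, d × √(3/16) = 0.30, so d = 0.693 SD in each. If the single arms are at 0.5 SD, the combined arm must reach 0.84 SD.

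**4. A slightly larger diet effect.** The protocol gives no figure; 0.6 SD is assumed here for illustration.
- 0 / 0.5 / 0.6 / 0.6: f = 0.249, power 63.4%.
- 0 / 0.5 / 0.6 / 0.7: f = 0.269, power 71.1%.
- 0 / 0.5 / 0.6 / 0.8: f = 0.295, power 79.5%.

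**5. One single-intervention arm versus control.** Two-sided t test, 32 versus 32, d = 0.5: noncentrality 0.5 / √(1/32 + 1/32) = 2.0; power 50.4%.

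**6. No dropout.** With all 148 evaluable, 0 / 0.5 / 0.5 / 0.5 gives 57.2%, and one arm versus control (37 versus 37) gives 56.4%.

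**7. Baseline adjustment.** If adjustment reduces the residual SD by √(1 − r²), the effective f is f / √(1 − r²). Reaching 0.30 needs r = √(1 − (f/0.30)²):
- from f = 0.25, r = √(1 − 0.694) = 0.55;
- from f = 0.217, r = √(1 − 0.521) = 0.69.

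**The case against.** The strongest reply is that nothing printed is false. The section claims 80% power for f = 0.30, and that is right. It never says that f = 0.30 equals 0.5 SD. The 0.5 SD is for exercise alone, diet may be slightly larger, and the combined arm is expected to do best; the section on combined exercise and diet even cites support for synergy. If effects are additive, f = 0.354 and 0.30 is cautious. The planned primary analysis is also an ANCOVA, which may have more power than the unadjusted ANOVA. Finally, a journal article may condense the derivation.

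Much of this stands. A reader might infer that 128 is a calculation error; it is not. A reader might infer that the trial is underpowered, or has only even odds of success. The documents do not support that as a general statement: 50% belongs to three equal active arms, whereas the stated hypothesis puts the combined arm ahead. Depending on the combined arm, power at 128 runs from 50% to 93% with both single arms at 0.5 SD.

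What does not stand is that these points establish the 80%. The hypotheses give an order, not a size, and the size decides the answer. A large combined-arm effect would raise omnibus power without helping the single-intervention comparisons. The Analysis section lists baseline cognitive performance only as a possible covariate, and no correlation is stated. As for condensation, the article prints both the justification and the input; the difficulty is that the two do not match as printed.

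A reader might also note that 64 versus 64 at 0.5 SD gives 80.1% and take that as the trial's power. That is a factorial contrast which the protocol does not plan. Under Analysis, Secondary outcomes, the two arms sharing an intervention are pooled against the control arm. That is 64 versus 32, with about 63% power at 0.5 SD, unadjusted.

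**Conclusion.** The point holds in a limited form. The 128 is arithmetically correct for f = 0.30, but the 80% is not established for the 0.5 SD effect cited in its support. With both single arms at 0.5 SD, the claim needs either about 0.84 SD in the combined arm or enough gain from baseline adjustment, and the protocol states neither. Each single-intervention comparison with control has about 50% power at 0.5 SD, whatever the combined arm does.

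These figures assume equal arms, 128 evaluable participants, independent observations, two-sided 5% for the pairwise test and no baseline adjustment. They do not show that power in the planned ANCOVA falls below 80%, only that the protocol gives no basis for that figure at the cited effect.

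**What to change.** Keep the sample size and reword the Sample size paragraph.
- State the four arm means, in SD units, behind f = 0.30: for example 0 / 0.5 / 0.5 / 0.84, or 0.69 SD in every active arm if they are assumed equal.
- Report the power for a 0.5 SD effect beside it: about 50% for the omnibus test with 0 / 0.5 / 0.5 / 0.5, and about 50% for one intervention arm versus control (32 versus 32), both unadjusted.
- If the ANCOVA is relied on to recover power, state the assumed correlation between baseline and 6 months. About 0.55 is needed from f = 0.25 and about 0.69 from f = 0.217.
- Do not present the 64 versus 64 figure as the power of the planned analysis unless that contrast is adopted.

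The cost is a rewritten paragraph and a less favourable stated power for some patterns of means. No participants are added.
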